## Abstract

**Background:**

Aceltylcysteine has been evaluated in several small trials as a means of reducing the risk of contrast-induced nephropathy (CIN), however systematic reviews of these studies do not provide conclusive answers. Therefore, a large randomized controlled trial (RCT) is needed to provide a reliable answer as to whether acetylcysteine is effective in decreasing the risk of CIN in high-risk patients undergoing angiographic procedures.

**Methods:**

ACT is a RCT of acetylcysteine versus placebo in 2,300 patients at-risk for CIN undergoing an intravascular angiographic procedure. The randomization list will be concealed. Participants, health care staff, investigators and outcome assessors will be blinded to whether patients receive acetylcysteine or placebo. All analysis will follow the intention-to-treat principle. The study drugs (acetylcysteine 1200 mg or placebo) will be administered orally twice daily for two doses before and two doses after the procedure. The primary outcome is the occurrence of CIN, defined as a 25% elevation of serum creatinine above baseline between 48 and 96 hours after angiography.

**Discussion:**

The first patient entered the trial on September, 2008. Up to April 7, 2009, 810 patients had been included in 35 centers. The mean age was 69 (Standard deviation: 10), 18% had a baseline serum creatinine >1.5 mg/dL, 57% were diabetics and 13% had a history of heart failure. The ongoing ACT Trial is the largest multicentre RCT that will determine whether acetylcysteine is effective in decreasing the risk of CIN in patients at risk undergoing angiography.

**Trial registration:**

Clinicaltrials.gov NCT00736866

## Background

Contrast-induced nephropathy (CIN) is a potentially serious complication of diagnostic and therapeutic procedures requiring intravenous administration of radiocontrast media. CIN is the third most common cause of new acute renal failure in hospitalized patients and is associated with the need of dialysis, prolonged hospital stay, increased health care costs and death[1,2]

The incidence of a rise in the serum creatinine of more than 50% above baseline or of more than 1 mg/dL is negligible in patients with normal renal function[3] However, patients with previous risk factors such as preexisting renal failure, diabetes, congestive heart failure, advanced age or concurrent administration of nephrotoxic drugs are at a much increased risk. [4] The incidence of CIN has been reported as 9 to 38% in patients with mild to moderate renal insufficiency and diabetes mellitus. [3,5] Patients requiring coronary intervention are another group at increased risk, with an overall incidence of acute renal failure (defined as a 25% increase in serum creatinine above baseline) of 14.4%. [2]

Optimal care to prevent CIN remains uncertain. [6] Patients with normal renal function and no other risk factors are at little risk and few measures are needed except for avoidance of volume depletion. For patients at increased risk the most well established measures are: 1) Avoidance of high osmolal agents[7]; 2) Avoidance of larger radiocontrast doses and repetitive studies (less than 48 hours apart); 3) Volume expansion with isotonic fluids[8] The infusion of isotonic sodium bicarbonate has been shown to be superior to isotonic saline to prevent CIN in most, but not all, randomized controlled trials. [9-12]

The role of acetylcysteine in preventing CIN has been evaluated in several randomized controlled trials and systematic reviews, being the most widely studied of all prophylaxis strategies. [13-16] Previous trials have low statistical power (median study size was 80 patients) and most failed to met quality standards such as allocation concealment, blinding, and intention-to-treat analysis. Similarly, systematic reviews and meta-analysis have found conflicting results. The most recent review, published by *Kelly et al*., included 26 randomized trials and found a protective effect of acetylcysteine (relative risk reduction of 38%), but with significant heterogeneity between the included trials (I^2 ^of 55%), meaning that 55% of the heterogeneity found could not be explained by chance alone. [16] This quite significant heterogeneity among studies' results prevents definitive conclusions to be drawn. An attempt to reveal the causes of heterogeneity using unsupervised clustering analysis revealed that a few smaller trials of average lower quality had similar very favorable results. [15] Removing these studies would leave another cluster of homogeneous trials with adequate quality showing neutral effect of acetylcysteine for preventing CIN. Besides methodological quality, differences in contrast media, outcome definitions, patient selection, dose and route of administration of acetylcysteine, and co-interventions may have contributed to the observed heterogeneity between trials.

Thus, the available evidence on the effects of acetylcysteine does not allow definitive conclusions about the efficacy of acetylcysteine for prevention of CIN. Moreover, it is not clear from previous evidence, what is the most effective dose of acetylcysteine, and what population benefits most from this intervention. A large randomized controlled trial, with high methodologic quality, involving several centers and with sufficient power to evaluate clinically relevant outcomes is needed to ultimately resolve whether acetylcysteine prevents CIN.

The ACT Trial is a randomized controlled trial to determine whether acetylcyteine reduces the risk for CIN in 2300 at-risk patients (ie, with previous renal failure or with other risk factors for contrast-induced nephropathy) undergoing an intravascular angiographic procedure. CIN is defined as an increase of 25% in serum creatinine measured between 48 to 96 hours compared to baseline. The ACT represents the largest trial conducted so far in this field.

## Methods

### Study Design

ACT is a randomized (concealed) controlled trial of acetylcysteine versus placebo in patients at-risk for CIN undergoing an intravascular angiographic procedure. Participants, health care staff, data collectors, outcome assessors, and statisticians will be blinded to whether patients receive acetylcysteine or placebo. All analysis will follow the intention-to-treat principle.

### Eligibility

The study population is comprised of patients at increased risk for CIN undergoing an angiographic procedure (coronary or peripheral arterial diagnostic intravascular angiography or percutaneous intervention). Therefore, risk factors for CIN such as previous renal failure, diabetes mellitus, heart failure, shock states and age greater than 70 years old were selected as the ACT study's inclusion criteria. [6] The Appendix presents the ACT trial's inclusion and exclusion criteria.

### Randomization and Allocation Concealment

Patients are randomized after providing a written informed consent in a 1:1 ratio to receive acetylcysteine or matching placebo. The random allocation list was generated in random permuted blocks of variable size (4, 6, 8 or 10) and was stratified by investigator centre. In order to guarantee concealment of the allocation list, randomization is implemented through a 24-hour web-based automated randomization system, making the sequence allocation totally unpredictable for the professionals responsible for entering the patients in the trial in each centre. The randomization list was generated and implemented by the The ACT study Clinical Data Management System (CDMS), a web based system that has been developed on a Microsoft SQL^® ^platform by a team of programmers of the Research Institute – Hcor, Sao Paulo, Brazil.

### Interventions

#### Study Drugs

The study drugs (acetylcysteine 1200 mg or matching placebo) will be administered orally twice daily for two doses before the procedure and two doses after the procedure (Figure 1). On occasion, when the patient is included in the study on the same day of the angiography, the pragmatic design of the ACT trial allows one dose to be administered at least 6 hours before the procedure and three doses after it.

**Figure 1 F1:**
[figure not shown]
**Flowchart of study drug administration**. Angiography may be done at any time between 6 hours after the first study drug dose to just before the 3^rd ^study drug dose.

#### Cointerventions

Hydration with 0.9% saline, 1 mL/kg/hour, starting 6–12 hours before angiography and continued for 6–12 hours after is strongly recommended for all patients. Changes in the total volume or flow may be needed according to attending physician, for example, for patients with signs of congestive heart failure.

All other decisions about management of patients are at the discretion of the responsible doctor, except that non-trial acetylcysteine will not be allowed during the trial period.

### Blinding

All study participants will be blinded to the assigned treatment, including patients, healthcare personnel, investigators and outcome assessors. The study statistician will be the only person able to access unblinded data, albeit she will not have any contact with participants and will not to carry any analysis according to study group before the database is locked.

The study drug, acetylcysteine or placebo, are packed in identical envelops. The envelop label contains information about the study drug and the treatment number. Each envelop contains 600 mg of oral powder acetylcisteine or placebo to be diluted in water. The powder and the solution in water are identical in appearance, taste and smell. In this regard, both are orange flavored.

### Outcomes

All outcomes of interest will be assessed in a blinded fashion. Data will be obtained at baseline, 48–96 hours and 30 days. The primary outcome of the ACT Trial is the occurrence of contrast-induced nephropathy (CIN), defined as a 25% elevation of serum creatinine above baseline between 48 and 96 hours after angiography. The secondary outcomes are: (1) A composite outcome of death, need of dialysis or a doubling in serum creatinine in thirty days; (2) A composite of death or need of dialysis in thirty days; (3) Individual components of the composite outcome.

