### Data Collection and Management

#### Baseline Data

The following data will be recorded at the baseline visit:

• Patient's initials, gender, date of birth;

• Inclusion and exclusion criteria;

• Relevant medical history: hypertension; use of non-steroidal anti-inflammatory within last 7 days; use of angiotensin converting enzyme inhibitors, diuretics, metformin; use of aminoglycosides, vancomycin, and other antibiotics;

• Serum creatinine: The most recent serum creatinine measured within the last three months will be recorded. When a recent creatinine measure is not available, a blood sample measurement will be drawn before angiography;

• Physical exam: arterial blood pressure and weight;

• Whether the patient undergone an angiographic procedure in the last 72 hours; if yes, the purpose (diagnosis or treatment), and whether any measure to prevent CIN was provided.

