#### Short-Term Follow-up Data

This is the main follow-up visit. Patients will have a serum creatinine measured between 48 and 96 hours after angiography for evaluation of the study primary outcome. Other data elements which will be recorded are:

• Administration of the third and fourth study drug doses; with details regarding timing and amount per dose;

• Hydration scheme after angiographic procedure: type of solution, total volume and duration of infusion;

• Whether the patient undergone an angiographic procedure within 72 hours after the index angiography; if yes, date, type, and measures to prevent CIN;

• Vital status; in case of deaths, date and cause;

• Need of dialysis.

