#### One month follow-up data

Research personnel will contact patients 30 days after the angiographic procedure and record the occurrence of:

• Angiographic procedure: date, type, measures to prevent CIN;

• Vital status; in case of deaths, date and cause;

• Need of dialysis.

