### Statistical Analysis Plan

All analysis will follow the intention-to-treat principle. The effect of acetylcysteine versus placebo on the primary endpoint, incidence of CIN between 48 to 96 hours, will be evaluated with a chi-square test. The magnitude of association will be presented as a risk ratio, with 95% confidence interval and number needed to treat (NNT). Statistical significance will be inferred using a significance level of 0.05.

Secondary outcomes evaluated 30 days after randomization will be presented as Kaplan-Meier curves according to the assigned treatment, and tested with the log-rank method. Hazard ratios and 95% confidence intervals will be calculated using non-adjusted Cox proportional hazards.

The incidence of the primary outcome will be analyzed in pre-specified subgroups using risk ratios and 95% confidence intervals. A subgroup effect will be inferred when the chi-squared test for homogeneity of effects is statistically significant. The following subgroups will be analyzed: 1) ≤70 year-old versus >70 year-old; 2) Male vs. female; 3) No previous renal failure vs. previous renal failure (serum creatinine >1.5 mg/dL); 4) Not diabetic vs diabetic; 5) Amount of contrast agent <140 mL vs. ≥140 mL. [17]

In the main trial publication, we also plan to include a random effects (DerSimonian-Laird) meta-analysis to combine ACT's results with those of previous randomized controlled trials evaluating acetylcysteine versus placebo for prevention of contrast-induced nephropathy. [18]

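### Creatinine doubling is defined over 30 days and planned for Kaplan-Meier/Cox analysis, but creatinine is scheduled only once after the procedure, at 48–96 hours

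*Protocol article*

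**What the plan says.** The Outcomes section gives the first secondary outcome as "A composite outcome of death, need of dialysis or a doubling in serum creatinine in thirty days". A second composite drops doubling, and the list ends with "Individual components of the composite outcome". Doubling is therefore both part of a composite and an outcome alone. The same section says "Data will be obtained at baseline, 48–96 hours and 30 days" without saying which data belong to which time.

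The data collection sections supply that detail:

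- **Baseline:** "The most recent serum creatinine measured within the last three months will be recorded"; if no recent value exists, blood is drawn before angiography.
- **Short-term follow-up**, which the article treats as its principal one: "Patients will have a serum creatinine measured between 48 and 96 hours after angiography for evaluation of the study primary outcome".
- **One month:** "Research personnel will contact patients 30 days after the angiographic procedure and record the occurrence of" three items, namely further angiography, vital status and need of dialysis. Creatinine is not among them.

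On analysis, the Statistical Analysis Plan section states: "Secondary outcomes evaluated 30 days after randomization will be presented as Kaplan-Meier curves according to the assigned treatment, and tested with the log-rank method". Unadjusted Cox models are to supply the hazard ratios.

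**The concern.** The definition and the analysis both assume that doubling is observed over 30 days and can be placed in time. The schedule looks for it once, in a two-day window near the start. Two consequences follow.

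First, a doubling that develops after the sample is counted as no event unless the patient also dies or needs dialysis. A reader of the trial report would take the 30-day figure to include later renal injury, and it would not.

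Second, a doubling seen at 48–96 hours is dated by when blood was drawn. The doubling curve would step over days 2–4 and then stay flat to day 30 because nothing was measured, not because nothing happened. The Cox model would treat those weeks as observed event-free time.

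This is the first-listed secondary outcome. The Discussion criticises earlier trials for not assessing outcomes that matter to patients, so the result is likely to be read closely.

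**Working it through.** **1. The plan's own figures.** No rate or sample size is given for the first composite or for doubling, so there is no stated figure to correct. The two sample sizes that are stated were checked to see whether this point reaches them. The formula, per arm, is

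n = [z(α/2)·√(2p̄(1−p̄)) + z(β)·√(p₁(1−p₁) + p₂(1−p₂))]² / (p₁−p₂)², with p̄ = (p₁+p₂)/2, 1:1 allocation, two-sided 5% and no continuity correction.

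- Primary outcome (Sample size section): p₁ = 0.15, p₂ = 0.15 × 0.70 = 0.105, 90% power. n = 1,153 per arm, 2,306 in total; the plan says 2,300.
- Death or dialysis (Data Monitoring Committee section): 3% versus 2%, 80% power. n = 3,826 per arm, 7,652 in total; the plan says 7,650.

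Both reproduce, and neither uses the doubling component.

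**2. What the schedule can observe.**

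| Component | Defined over | Where it is recorded | Time information listed |
|---|---|---|---|
| Death | 30 days | both follow-ups | date of death |
| Dialysis | 30 days | both follow-ups | occurrence; no date listed |
| Creatinine doubling | 30 days | 48–96 h sample only | time of sampling |

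**3. Size of the gap.** Counted from angiography, the latest permitted sample is at 96/24 = 4 days. Days without a scheduled creatinine: 30 − 4 = 26, and 26/30 = 87%. For a sample at 48 hours the gap is 30 − 2 = 28 days, or 93%.

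The analysis section counts from randomization, and the interval from randomization to angiography is not stated. Assuming one day, the latest sample falls on day 5, leaving 30 − 5 = 25 days, or 83%. The conclusion does not depend on which origin is used.

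**4. What the time-to-event analysis of doubling would contain.** Every patient has at most one observation, between day 2 and day 4 after angiography. Event status is yes or no at that sample. Differences in event time between two patients with doubling reflect only when each was sampled. The information is that of a binary outcome at one visit, which is how the plan already treats the primary outcome from the same sample (chi-square test, risk ratio).

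**5. What can be estimated.** With baseline and 48–96 hour creatinine both recorded, the proportion with doubling at that sample is available. So is the proportion with death or dialysis by day 30, or doubling at that sample.

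**The case against.** **The article is condensed, and a 30-day creatinine may be in the full protocol.** This carries little weight. The one-month section itemises what is recorded and describes a contact by research personnel. A blood sample is a study procedure, not a form detail. The general statement that data are obtained at 30 days does not name creatinine.

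**A laboratory endpoint can enter a Kaplan-Meier or Cox analysis at its sampling time.** This is correct. Both arms share one blinded schedule, so the coarse timing does not by itself favour either arm. A number can be produced. The fault is that it would carry a 30-day time-to-event label for what is a day 2–4 binary result.

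**A reader might infer that dialysis is also undatable, so that both composites, dialysis and doubling all fail.** Both follow-up lists name dates for deaths ("Vital status; in case of deaths, date and cause" at one month) and for further angiography, but not for dialysis. A short bullet in an article does not show that the form lacks the field, so this is a point to confirm and not a finding. Exact dates would also matter little to the effect size. At the plan's 3% versus 2%, the risk ratio is 0.02/0.03 = 0.667 and the constant-hazard ratio is ln(0.98)/ln(0.97) = 0.663.

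**A reader might also infer that follow-up is lost because analysis runs from randomization and contact from angiography.** Angiography follows randomization, so a contact 30 days after angiography already covers 30 days from randomization.

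**Conclusion.** The point holds for two secondary outcomes: the first composite and creatinine doubling alone. Their 30-day definition and time-to-event analysis do not match a schedule with one post-procedure creatinine at 48–96 hours. At least 26 of the 30 days after angiography are unmeasured for doubling.

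The documents do not support saying that these outcomes cannot be estimated at all, that the arms would be compared unfairly, or that most of the secondary outcomes fail. Death, dialysis and death-or-dialysis are not shown to be affected. The primary outcome, its test and the sample size are untouched, so this is a should-fix matter.

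The conclusion assumes that the itemised one-month list is complete as regards blood sampling. How many doublings arise after 96 hours cannot be judged from the documents, so no numerical effect on the result is claimed.

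**What to change.** **Outcomes section.** Define the component as doubling of serum creatinine over baseline at the 48–96 hour sample. State the first composite as death or need of dialysis by day 30, or doubling at the 48–96 hour sample.

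**Statistical Analysis Plan section.** Compare the first composite and the doubling component as proportions, with a risk ratio, 95% confidence interval and chi-square test as for the primary outcome. Keep Kaplan-Meier, log-rank and Cox for death, dialysis and death-or-dialysis.

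**Minor check.** Confirm that the follow-up forms record the date of first dialysis.

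**Cost.** Wording in two sections, with no added visit or sample. The price is that the outcome no longer claims to capture renal injury after 96 hours, which the schedule does not measure anyway. Adding a 30-day creatinine would be the alternative if that claim is wanted. It would need a new sample, could not be obtained at day 30 for those among the 810 already randomized who have passed that point, and would still give a visit time and not an event time.

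**Timing.** The Blinding section rules out analysis by group before database lock, so the change can be made without knowledge of results.

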### Data Collection and Management

#### Baseline Data

The following data will be recorded at the baseline visit:

• Patient's initials, gender, date of birth;

• Inclusion and exclusion criteria;

• Relevant medical history: hypertension; use of non-steroidal anti-inflammatory within last 7 days; use of angiotensin converting enzyme inhibitors, diuretics, metformin; use of aminoglycosides, vancomycin, and other antibiotics;

• Serum creatinine: The most recent serum creatinine measured within the last three months will be recorded. When a recent creatinine measure is not available, a blood sample measurement will be drawn before angiography;

• Physical exam: arterial blood pressure and weight;

• Whether the patient undergone an angiographic procedure in the last 72 hours; if yes, the purpose (diagnosis or treatment), and whether any measure to prevent CIN was provided.

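### For patients with no recent creatinine, the baseline sample is tied to angiography rather than to the first dose, so the primary-outcome denominator may be measured after treatment has started

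*Protocol article*

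**What the plan says.** All sections cited are in the protocol article.

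- **Default baseline** (Baseline Data): "The most recent serum creatinine measured within the last three months will be recorded".
- **Fallback baseline** (same bullet): "When a recent creatinine measure is not available, a blood sample measurement will be drawn before angiography". Angiography is the only time limit stated. The list is introduced by "The following data will be recorded at the baseline visit", but that visit is not timed against randomisation, dosing or hydration.
- **Use of the value** (Outcomes): the primary outcome is CIN, "defined as a 25% elevation of serum creatinine above baseline between 48 and 96 hours after angiography". The Statistical Analysis Plan section also defines a subgroup by serum creatinine above 1.5 mg/dL.
- **Dosing before the procedure** (Study Drugs): study drug "will be administered orally twice daily for two doses before the procedure and two doses after the procedure". For same-day inclusions the design "allows one dose to be administered at least 6 hours before the procedure and three doses after it". The Figure 1 caption agrees: "Angiography may be done at any time between 6 hours after the first study drug dose to just before the" third dose.
- **Hydration before the procedure** (Cointerventions): "Hydration with 0.9% saline, 1 mL/kg/hour, starting 6–12 hours before angiography" is strongly recommended for all patients, and the attending physician may adjust it.

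**The concern.** In a change-from-baseline endpoint, randomisation protects the comparison only if the baseline precedes treatment. Here treatment starts at least 6 hours before angiography, yet the fallback sample is limited only by angiography. A site that takes blood on the patient's arrival for the procedure has met the rule as written, but its baseline follows randomisation, one or two doses, and part or all of the pre-procedure saline.

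Two consequences are possible in these patients. First, if saline lowers creatinine, the denominator is too low in both arms, and a mere return to the pre-hydration level counts towards the 25% rise. Second, if the active drug changes early creatinine or fluid balance, the denominator differs by arm and the risk ratio is biased. The renal-failure subgroup could also rest on a post-randomisation value where no earlier creatinine exists.

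This concerns samples taken too late. Whether a three-month-old value is an adequate baseline is a separate question.

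**Working it through.** **1. Timing, from the documents.** Angiography falls between 6 hours after dose 1 and just before dose 3. If twice daily means every 12 hours (an inference), that is 6 to about 24 hours after dose 1. Saline at 1 mL/kg/h for 6 to 12 hours gives 6 to 12 mL/kg before the procedure. A sample taken just before angiography can follow all of this. No section requires it to precede randomisation, dose 1 or saline.

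**2. The plan's own sample size.** Control rate 15%, relative risk reduction 30% (10.5% on active), 90% power, two-sided 5%. Unpooled formula: (1.960 + 1.282)² × (0.15×0.85 + 0.105×0.895) / 0.045² gives 1,150 per arm, or 2,300 in total. The stated figure is reproduced and is not in dispute. Power at 1,150 per arm is 89.9%.

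**3. Illustrative model (assumptions, not in the documents).** Log(follow-up/baseline creatinine) is normal. In controls the mean is 0 and the SD is set so that 15% exceed a 25% rise: SD = ln(1.25)/z(0.85) = 0.2231/1.0364 = 0.215. In the active arm the mean is shifted so that 10.5% exceed it. If the late baseline is lower by a fraction s, the control rate is P(Z > (ln 1.25 + ln(1−s))/SD):

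- s = 2%: 17.3%
- s = 3%: 18.5%
- s = 5%: 21.2%

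For the active arm, s = 3% moves 10.5% to 13.3%. These rates apply to affected patients only. With affected share f, each arm's rate is (1−f) × original + f × shifted.

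**4. Equal shift in both arms (saline), s = 3%, f = 25%.**

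- Control: 0.75×15.0% + 0.25×18.5% = 15.9%
- Active: 0.75×10.5% + 0.25×13.3% = 11.2%
- Risk ratio 0.705, against a true 0.70; power 90.7%
- NNT 1/0.0468 = 21.4, against 1/0.045 = 22.2

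**5. Shift in the active arm only, s = 3% (a hypothetical drug effect).**

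| Share affected | True RR 0.70 reads | Power | True RR 1.00 reads |
|---|---|---|---|
| 2% | 0.704 | 89% | 1.005 |
| 5% | 0.709 | 88% | 1.01 |
| 10% | 0.72 | 86% | 1.02 |
| 25% | 0.75 | 77% | 1.06 |
| 50% | 0.79 | 59% | 1.12 |

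**6. Opposite direction.** If the late baseline were 3% higher on active drug only, the shifted rates are P(Z > (ln 1.25 + ln 1.03)/0.215) = 12.0% from 15%, and 8.2% from 10.5%. At f = 25%, a true 0.70 reads (0.75×10.5% + 0.25×8.2%)/15% = 0.66, and a true null reads (0.75×15% + 0.25×12.0%)/15% = 0.95. The bias then favours the drug.

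**7. Sensitivity to the SD.** With SD 0.15 to 0.20, a share of 10% to 30% and a one-arm lowering of 2% to 5%, a true 0.70 reads 0.71 to 0.85. The result depends strongly on inputs that nobody can read from the documents.

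**The case against.** The layout points to a pre-treatment draw. The bullet stands in a list for the baseline visit, next to eligibility, history, blood pressure and weight, while doses 1 and 2 and pre-procedure saline are recorded separately under Treatment Data. The full protocol or case report form, not shown, may carry a sample-time field or a tighter rule. This stands in part: a pre-dose draw may well be intended, and the absence of a time field cannot be established from an article. But the article does state a timing rule for this sample, and the event it names is angiography. The untimed visit heading does not override that.

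The affected group is also limited to patients with no creatinine in three months who are then sampled after dose 1. Neither share is given, and both may be small. This stands.

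A reader might infer from the 25% row of the one-arm table that the trial will report about 0.75 for a true 0.70 and lose 13 points of power. The documents do not support that. It stacks an arbitrary share on a 3% creatinine lowering by acetylcysteine alone, and no section reports such an effect. The pre-procedure exposure that the documents describe for both arms is saline, which leaves the risk ratio almost unchanged. The one relevant drug reaction listed on the adverse events form, emesis, would more plausibly raise creatinine through volume loss, which is the opposite direction.

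The subgroup consequence is minor. A 3% shift reclassifies only patients with a true value of about 1.50 to 1.55 mg/dL (1.50/0.97 = 1.546), in one of five subgroups.

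**Conclusion.** The point holds as a flaw in a stated rule: the fallback baseline is anchored to the wrong event, so a compliant sample can be a post-randomisation, post-dose value. It does not show that such samples are common or that the primary comparison is materially biased.

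Size depends on two unknowns. If only saline acts, and acts equally in both arms, the CIN rate is inflated (15.0% to 15.9% at a 3% shift in 25% of patients), the NNT moves slightly, and the risk ratio barely changes. Bias between arms arises only if the study drug alters early creatinine or fluid balance, and it could go either way. With a 3% one-arm lowering and 2% to 5% of patients affected, power falls by about 1 to 2 points. Larger losses need larger shares or shifts, for which the documents give no basis. The sample size of 2,300 is unaffected. The change is worth making because it is nearly free and removes the question from the primary endpoint.

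**What to change.** - **Baseline Data:** state that, when no creatinine from the last three months exists, the sample is drawn before the first dose of study drug and before study hydration starts. Record the date and time of the sample that serves as baseline.
- **Statistical Analysis Plan, renal-failure subgroup:** define membership from that pre-dose value.
- **Patients already enrolled (810 at the time of the article):** where sample times can be retrieved, for example from laboratory records, flag baselines drawn after the first dose and add a sensitivity analysis without them. The article does not list sample time among the data collected, so this may be possible for only some patients. The intention-to-treat analysis of all patients stays primary.

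**Cost:** one sentence in an amendment and date and time fields. It is the same blood draw taken some hours earlier, with no extra sample and no change in sample size. The small downside is that same-day inclusions need blood taken, though not yet reported, before dosing. If the full protocol already requires a pre-dose draw, only the article's wording needs to be aligned with it.
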